### Data collection and management

2.13

An Electronic Data Capture (EDC) system will collect the clinical data of the participants. Two trained investigators will enter and reconcile data independently to maintain accuracy. They will complete the Case Report Form (CRF) for each participant. A research assistant will then verify the data accuracy and integrity, and address errors, omissions, or the need for clarification. A dedicated data administrator will oversee the system without data modification or access until participant enrolment, observation, and data collection are completed. In the CRFs, investigators will indicate changes by drawing lines, record modified data, as well as sign and date without erasing or overwriting original records. Both paper and electronic records will be stored for at least five years post-publication. Biospecimens will be ethically disposed after monitoring and in accordance with the participant rights and interests. Regular database backups will be implemented to prevent loss of data. To ensure participant confidentiality and prevent information leakage, personal details such as names, phone numbers, ID numbers, and medical history will be anonymous.

### Quality control and assurance

2.14

The trial protocol has undergone rigorous review by the experts in acupuncture, cardiovascular medicine, statistics, and methodology. Investigators will be identified post-eligibility screening and a consistent staff will be maintained throughout the study. All the researchers, including acupuncturists, evaluators, and statisticians will receive pre-initiation training for consistently implementing the protocols. Regular meetings will be held to review the study progress, address any issues, and ensure protocol adherence. Laboratory tests will follow standard operating requirements with prompt explanations for any changes during the study. Licensed acupuncturists with over two years of experience will administer acupuncture treatment exclusively while avoiding other therapies such as acupressure and moxibustion. Furthermore, experts will supervise and guide the operators throughout the procedures, and promptly address any issues that may arise and ensure the smooth progression of surgeries. High patient compliance will be ensured because of the nature of the emergency surgery, and will be supported by drug counting, regular checks, compensation, and health education. The reasons for dropouts and withdrawals, if any, will be carefully documented. While improving patient compliance, researchers will strictly limit the inclusion criteria and use fully randomized, blinded, and concealed assignments. Efficacy and safety indicators will be evaluated and documented by independent assessors who are unaware of the group assignments. Medical records will be strictly confidential, with anonymous data processing. The data will be accessible only to the authorized researchers and the sponsor representatives. Throughout the trial, all the investigators will adhere to strict confidentiality policies.

### Statistical analysis

2.15

Statistical analysis will be performed according to the intention-to-treat (ITT) principle using the SPSS V.25.0 software (IBM Corporation, Armonk, New York, USA). Missing data will be addressed through multiple imputations. *P* < 0.05 will be considered as a statistically significant difference between groups. The normally distributed data will be presented as Mean ± SEM. The inter-group comparisons for this data will be performed using the independent sample t-tests and paired t-tests will be used within-group comparisons. Non-normally distributed data will be presented as median (interquartile range) and the independent sample non-parametric tests will be performed for comparing the data between group. Count data will be expressed as frequency (percentage) and analyzed using the chi-square test. Ridit analysis or rank sum tests will be used to assess the ordinal data.

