### Calculation of sample size

2.12

Since previous RCTs have not investigated acupuncture as an adjunct intervention for managing SF-NR in the AMI patients during PCI, it is challenging to determine the optimal sample size through power calculation. Therefore, instead of a formal sample size estimation, this trial will use a preliminary exploratory clinical pilot design for estimating the sample size (47). However, to preliminarily assess the feasibility of acupuncture-assisted PCI to prevent SF-NR, we will meticulously ensure adequate number of participants in our experimental design by adhering to the established guideline of a minimum of 12 participants per group for pilot studies (48). A previous study suggested that each group should have a sample size ranging from 20 to 25 cases for exploratory clinical trials assessing the effectiveness of intervention measures (49). Therefore, in this study, each group consisted of 25 patients and a total of 50 cases for the 2 groups. However, to account for a dropout rate of 20%, this study will recruit 60 patients (30 patients per group). It seems plausible that the dropout rate would be less than 20% because of the short duration of the procedure and the high requirement of surgery among the participants (50). The results of this study will contribute to providing the effect size data for calculating sample sizes in the further large-scale RCTs.

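### Multiple imputation is paired with chi-square and rank tests that give no directly poolable estimate and no effect size, in a pilot meant to supply effect sizes

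*Protocol article*

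**What the plan says.** All the relevant rules stand in section 2.15 (Statistical analysis) of the protocol article. "Statistical analysis will be performed according to the intention-to-treat (ITT) principle", and "Missing data will be addressed through multiple imputations". The significance rule is P "< 0.05 will be considered as a statistically significant difference between groups".

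The between-group tests are named by type of data:

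- Counts: "Count data will be expressed as frequency (percentage) and analyzed using the chi-square test". This covers the primary outcome, incidence of SF-NR (section 2.9.1), and MACCE at one month.
- Non-normal measurements: "the independent sample non-parametric tests will be performed for comparing the data between group".
- Ordinal data: "Ridit analysis or rank sum tests will be used to assess the ordinal data".
- Normal measurements: "The inter-group comparisons for this data will be performed using the independent sample t-tests".

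The section names no effect estimate for SF-NR and no way of combining results across imputed data sets. Section 2.12 raises the target from 50 to 60 patients "to account for a dropout rate of 20" per cent, expects actual dropout to be lower, and says the results are to feed the sample size calculation of larger trials.

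**The concern.** Multiple imputation produces several completed data sets. Rubin's rules combine them through an estimate and its standard error, and add the variation between imputations to the variance. A t-test brings both quantities with it. A chi-square or rank sum test returns only a statistic and a P value, so an analyst following section 2.15 literally has one P value per imputed set and no stated route to a single result.

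Two things are at stake. First, an analyst who improvises may test one imputed set, average the statistics or test the stacked file. Each leaves out some or all of the imputation uncertainty. Second, whatever is done about missing data, the named tests do not deliver the effect size with its precision that section 2.12 gives as a purpose of the pilot.

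**Working it through.** **Inputs from the documents.** 30 patients per arm and 20% dropout (section 2.12); nominal 0.05 (section 2.15), taken as two-sided; null event rate 41% (Introduction). The plan's recruitment figure reproduces as 50 × (1 + 0.20) = 60.

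**Assumptions.** Five imputations, data missing completely at random, proper imputation within arm (beta-binomial for SF-NR, normal for the rank test), uncorrected chi-square. The documents give none of these. Missingness was varied over 2, 5, 10 and 20%.

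**Rules that pool validly, with M imputations.**

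- Rubin's rules: the pooled estimate is the mean of the M estimates, with variance T = W + (1 + 1/M)B. W is the mean within-set variance and B the variance between sets. With M = 5 the factor on B is 1.2.
- D2, for one-degree-of-freedom chi-squares d: r = (1 + 1/M) × variance of √d. D2 = [mean(d) − r(M + 1)/(M − 1)]/(1 + r), referred to F with 1 and (M − 1)(1 + 1/r)² degrees of freedom.

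**Simulated type I error for SF-NR (100,000 null trials per setting, event rate 41%, M = 5).**

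| Method | 20% missing | 10% | 5% | 2% |
|---|---|---|---|---|
| Chi-square on one imputed set | 10.9% | 7.5% | 6.3% | 5.5% |
| Mean chi-square | 9.6% | 7.0% | 6.2% | 5.6% |
| Median P | 9.0% | 6.8% | 6.1% | 5.5% |
| Mean P | 6.6% | 5.7% | 5.5% | 5.3% |
| Smallest P | 22.6% | 13.6% | 9.5% | 6.8% |
| Stacked file | 45.0% | 42.0% | 40.7% | 39.2% |
| D2 | 5.1% | 5.0% | 5.2% | 5.1% |
| Rubin, risk difference, pooled-variance SE | 5.5% | 5.2% | 5.3% | 5.2% |
| Rubin, risk difference, unpooled SE | 6.2% | 6.0% | 6.1% | 5.8% |
| Observed cases only | 5.3% | 5.2% | 5.4% | 5.2% |

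At an event rate of 20% the results are nearly the same. With 20 imputations the stacked file reaches 67 to 70%.

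**Check by formula.** Set the complete-data variance to 1. With a fraction f missing, the observed-data variance is 1/(1 − f), so the between-imputation variance is B = 1/(1 − f) − 1.

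- One imputed set: true variance 1/(1 − f) + B, but the test assumes 1. At f = 0.20 this is 1.25 + 0.25 = 1.50. Then 1.96/√1.50 = 1.600, a two-sided error of 11.0% (simulated 10.9%). At f = 0.10: 1.111 + 0.111 = 1.222, giving 7.6% (7.5%). At f = 0.02: 1.0408, giving 5.5% (5.5%).
- Stacked file, M = 5: the mean estimate has variance 1.25 + 0.25/5 = 1.30, but the test assumes 1/5, a ratio of 6.5. Then 1.96/√6.5 = 0.769, an error of 44% (simulated 45%). With nothing missing the ratio is 5 and the error is still 38%, because each patient is counted five times.

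**Rank sum test (20,000 null trials, 20% missing, M = 5).** One set 10.5%, mean chi-square 8.7%, median P 8.4%, stacked 44.0%, D2 4.5%, Rubin's rules on the standardized statistic 4.9%, observed cases 4.8%. At 3.3% missing, one set gives 5.7% and the mean chi-square 5.6%.

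**The case against.** A reader might infer that multiple imputation and these tests cannot be combined validly. That is wrong. D2 holds about 5% for both kinds of test, and the 2×2 table behind the chi-square yields a risk difference with a standard error. A Ridit analysis can likewise supply a mean ridit and its standard error, although the plan allows a rank sum test in its place.

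A reader might also infer that the trial will run at an error rate of 9 to 11%, or even 45%. The documents do not support this. No section proposes testing one set, averaging statistics or stacking. A pooling rule, the number of imputations and the imputation model are commonly left to an analysis plan, which is not shown, so their absence is not an error.

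The 20% setting is also harsh for the primary outcome. SF-NR is read immediately after stent implantation (section 2.9.1), and section 2.12 thinks dropout below 20% plausible. At 2% missing, the single-set, mean and median shortcuts give 5.5 to 5.6%. Nor is the gain in error control always large: at 10% missing the unpooled risk difference runs at 6.0%, against 6.8 to 7.0% for the median and mean shortcuts. Finally, this is an exploratory pilot without a formal power calculation.

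All of this stands, and it limits the point. It does not answer the mismatch between tests that return no effect size and a pilot meant to supply one. It also has less force for outcomes read later, such as biomarkers at 12 h and 72 h and MACCE at one month, where more loss is plausible.

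**Conclusion.** The point holds as a poor fit between the named tests, the named missing-data method and the stated purpose of the pilot. It does not show that the plan inflates its type I error.

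The risk left open is conditional on an analyst's shortcut. Testing one set or using the mean or median statistic costs about 9 to 11% at 20% missing and about 7 to 7.5% at 10%, and is close to nominal at 2%. Only the stacked file is severe at every level, at 39 to 45% with five imputations. These sizes rest on the assumed imputation model, five imputations and values missing completely at random. The documents give no missingness figure for SF-NR, so its low level is a judgement from when it is read. Severity is minor to moderate.

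**What to change.** Amend section 2.15, or settle it in the analysis plan before data are analysed:

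1. **SF-NR:** report the risk difference with its 95% confidence interval, or fit a logistic model with treatment and the stratification factors in section 2.6 (gender, age, ST-segment elevation).
2. **Cardiac and inflammatory biomarkers:** use regression on treatment adjusted for the preoperative value, on the log scale where skewed. Table 1 already schedules the preoperative measurements.
3. **Imputed data:** pool these estimates by Rubin's rules. If a chi-square or rank test is kept on imputed data, pool its statistic by a valid rule such as D2, and state that the stacked file will not be tested.

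The cost is a change of wording and code, with no extra patients or measurements. One limit should be accepted knowingly: at 30 per arm the risk difference with unpooled variance runs slightly above nominal, at about 6%. The pooled-variance standard error gives 5.2 to 5.5% when used for the test.

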**Figure 1 F1:**
[figure not shown]
Flow chart of the trial.

**Table 1 T1:** Study design schedule.

Study period	Treatment period			Follow-up period		
Timepoint	Preoperative PCI	Intraoperative PCI	Postoperative PCI	Postoperative		
				12 h	72 h	1 M
Demographic data^a^	√					
Routine drug treatment	√	** **	√	** **	** **	** **
Acupuncture (left Neiguan with Ximen)	** **	√	** **	** **	** **	** **
Incidence of Slow flow/no-reflow (TIMI and CTFC)	** **	√	** **	** **	** **	** **
Changes in cardiac biomarkers^b^	√	** **	** **	√	√	** **
Inflammatory markers^c^	√	** **	** **	√		** **
Pain score (NRS)	√	** **	√	√	** **	** **
VAS-A scores	√		√	√	** **	** **
Electrocardiogram	√	** **	√	√	** **	** **
TCM symptom score	√	** **	** **	** **	√	** **
MACCE	** **	** **	** **	** **	** **	√
Adverse events	√	√	√	√	√	√
Safety assessments^d^	√	** **	** **	** **	√	

^a^
Including age, gender, BMI, smoking history, medical history, and symptom duration.

^b^
Including cTnI, Myo, CK-MB, NT-proBNP.

^c^
Including leukocytes, neutrophils, lymphocytes, and Hs-CRP.

^d^
Including blood routine, electrolytes, liver and renal functions.

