#### Secondary outcomes

2.9.2

(1)*Cardiac biomarkers*: Assessments of serum high-sensitive cardiac troponin I (cTnI), myoglobin (Myo), creatine kinase-MB (CK-MB), and N-terminal pro-brain natriuretic peptide (NT-proBNP).(2)*Inflammatory biomarkers*: Assessments of leukocytes, neutrophils, lymphocytes, and high-sensitivity C-reactive protein (Hs-CRP).(3)*Chest pain score*: Chest pain severity will be assessed using the Numeric Rating Scale (NRS) with the participants rating pain on a 10-point scale, where 0 represents no pain, 1–3 indicates mild pain, 4–6 moderate pain, and 7–10 indicates severe pain.(4)*Anxiety score*: This will be evaluated using the Visual Analogue Scale for Anxiety (VAS-A) with 10-point scoring system where 0 indicates no anxiety, 1–3 indicates mild anxiety, 4–6 indicates moderate anxiety, and 7–10 indicates severe anxiety.(5)*Electrocardiogram examination*: Assessment of cardiac activity using the electrocardiograms.(6)*TCM symptom score*: Symptom severity grading will be based on the 2002 Guidance principle of clinical research on new drugs of Traditional Chinese Medicine (46). The severity grading categories are none, mild, moderate, and severe. Major symptoms will be scored as 0, 3, 6, or 9 points. The secondary symptoms will be scored as 0, 1, 2, or 3 points. The specific scores are shown in the Supplementary Material. TCM symptom score = major symptoms score + secondary symptoms score. The efficacy index will be calculated using the following formula: [(Score at initial admission - Score at 24 h after PCI)/Score at initial admission] × 100%. The efficacy index is classified into the following three grades: ineffective (0%–30%), effective (30%–70%), and significant (70%–100%). Total effective rate = significant effective rate + effective rate.(7)*MACCE*: The incidences of major adverse cardiovascular and cerebrovascular events (MACCE) include hemorrhage, recurrent myocardial infarction, revascularization, readmission, and cardiogenic death during the follow up within one month after PCI.

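### The planned between-arm tests of the continuous secondary outcomes use no baseline covariate; they are paired with within-arm tests that compare no treatments and, for normal data, with mean ± SEM

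*Protocol article*

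**What the plan says.** Section 2.15 fixes the methods by type of data:

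- **Normally distributed data.** Summary: "The normally distributed data will be presented as Mean ± SEM". Tests: "The inter-group comparisons for this data will be performed using the independent sample t-tests and paired t-tests will be used within-group comparisons".
- **Other continuous data.** "Non-normally distributed data will be presented as median (interquartile range) and the independent sample non-parametric tests will be performed for comparing the data between group".
- **Missing values.** "Missing data will be addressed through multiple imputations".

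No covariate is named for any between-arm comparison, and section 2.15 does not say whether the tests use follow-up values or changes from baseline.

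Three other places bear on this:

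- **Table 1** ticks the preoperative column for cardiac biomarkers, inflammatory markers, the pain score, VAS-A and the TCM symptom score. It labels the first of these "Changes in cardiac biomarkers".
- **Section 2.6** stratifies the randomisation by variables such as gender, age and ST-elevation infarction.
- **Section 2.12** gives a purpose of the pilot: "The results of this study will contribute to providing the effect size data for calculating sample sizes".

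**The concern.** Three stated choices fit the purpose of the pilot poorly.

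1. **No baseline adjustment between arms.** The preoperative values and stratification factors are collected but enter no stated between-arm test as covariates. With 25 to 30 patients per arm, variation that the baseline could explain stays in the error term, and a chance difference at baseline stays in the estimate.
2. **Within-arm paired t-tests.** Both arms receive PCI and routine drug treatment (sections 2.8.1 and 2.8.2), so a change over time can occur without any effect of electroacupuncture. A significant change in one arm and not in the other is not a comparison of the arms. Section 2.15 does not say what these tests are for.
3. **SEM as the data summary.** The SEM describes the precision of a mean, not the spread between patients. Planning a later trial on a continuous outcome needs the spread.

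At stake are wider intervals than necessary, a within-arm result that may be read as a treatment effect, and summaries that are awkward for planning the next trial.

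**Working it through.** **Inputs from the protocol article.** Section 2.12 gives 25 patients per arm as the target and 30 per arm recruited (25 × 1.2 = 30). Both sizes are used below. Section 2.15 gives a 0.05 significance level; two-sided testing is assumed. The article gives no SD, correlation or power for any continuous outcome, so there is no figure of its own to reproduce on this point.

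**Assumptions.** The baseline-outcome correlation r is taken as 0.3, 0.5 and 0.7, with equal SD at baseline and follow-up. All differences are in units of that SD.

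**Step 1. Variance of the between-arm comparison, relative to a t-test on follow-up values**

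| r | ANCOVA, 1 − r² | Change score, 2(1 − r) | ANCOVA ÷ change, (1 + r)/2 |
|---|---|---|---|
| 0.3 | 0.91 | 1.40 | 0.65 |
| 0.5 | 0.75 | 1.00 | 0.75 |
| 0.7 | 0.51 | 0.60 | 0.85 |

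ANCOVA therefore cuts variance by 9%, 25% and 49% against follow-up values, and by 35%, 25% and 15% against change scores. It gains on both readings of section 2.15 over this whole range.

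The difference detectable with 80% power is (1.96 + 0.84) × √(2/n) × √(1 − r²). The power column is for an assumed true difference of 0.6 SD (normal approximation).

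| Analysis | Detectable, n = 25 | Detectable, n = 30 | Power, n = 25 | Power, n = 30 |
|---|---|---|---|---|
| t-test on follow-up | 0.79 | 0.72 | 56% | 64% |
| ANCOVA, r = 0.3 | 0.76 | 0.69 | 60% | 68% |
| ANCOVA, r = 0.5 | 0.69 | 0.63 | 69% | 77% |
| ANCOVA, r = 0.7 | 0.57 | 0.52 | 84% | 90% |

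The chance difference in baseline means has a standard deviation of √(2/n): 0.28 SD at 25 per arm and 0.26 SD at 30.

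These figures are for normally distributed data, or data made so by a log scale. They ignore the few degrees of freedom spent on covariates. The gain over a rank test was not computed.

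**Step 2. Within-arm paired tests when there is no treatment effect**

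Let both arms truly change by the same amount, with r = 0.5. The SD of the within-patient change is then √(2 × 0.5) = 1. If p is the power of one paired t-test (non-central t), exactly one arm is significant with probability 2p(1 − p).

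| True change in both arms (SD) | p, n = 25 | Exactly one, n = 25 | p, n = 30 | Exactly one, n = 30 |
|---|---|---|---|---|
| 0.2 | 0.161 | 27% | 0.185 | 30% |
| 0.3 | 0.302 | 42% | 0.355 | 46% |
| 0.4 | 0.484 | 50% | 0.563 | 49% |
| 0.5 | 0.670 | 44% | 0.754 | 37% |

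The maximum of 2p(1 − p) is 50%, reached at p = 0.5. When changes are large the figure falls: at p = 0.95 it is 2 × 0.95 × 0.05 = 9.5%.

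**Step 3. SEM and SD**

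SD = SEM × √n, so the ratio is √25 = 5.0 and √30 = 5.48. With complete data the SD is recovered exactly; after multiple imputation only approximately.

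To show the scale of a misreading: a trial for 0.5 SD with 80% power needs 2 × (1.96 + 0.84)² ÷ 0.5² = 63 per arm. Taking the SEM at n = 30 for the SD divides this by 30 and gives 3 per arm after rounding up.

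**The case against.** The other side has real points, and they limit the finding.

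- **Scope.** A reader might infer that every continuous outcome is to be tested by t-test and shown as mean ± SEM. Section 2.15 limits both to normally distributed data; anything non-normal goes to medians and non-parametric tests. What stands is that neither branch names a baseline covariate.
- **Baselines are not ignored.** The paired tests use them, the TCM efficacy index in section 2.9.2 is relative to the admission score, and the Table 1 label for cardiac biomarkers may mean that changes are compared. What is missing is baseline as a covariate between arms. If changes are compared, the gain at r = 0.7 is 15%, not 49%.
- **Validity.** A reader might infer a false-positive problem in the between-arm tests. There is none: under randomisation the unadjusted test is valid, and chance imbalance is already in its standard error. Stratification may also limit some of that imbalance.
- **Paired tests.** Section 2.15 ties its significance threshold to differences between groups and never calls a within-arm result evidence of effect. The harm depends on how results are later read, and 50% is the worst case. Still, the tests answer no treatment question and are not labelled descriptive.
- **SEM.** It is labelled as SEM and can be converted, so the SD is not lost. A badly undersized next trial needs someone to misread the label.
- **Primary outcome.** It is binary. A later trial sized on the incidence of slow flow or no-reflow needs event rates, not an SD.

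These objections narrow the point but do not remove it.

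**Conclusion.** The point holds for the continuous secondary outcomes and is of modest weight. These are methods stated in section 2.15, not details left to an unseen analysis plan.

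The loss from the unadjusted tests is precision, not type I error. Its size rests on an assumed correlation of 0.3 to 0.7: a variance reduction of 9% to 49% forgone if follow-up values are tested, or 35% to 15% if changes are tested.

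The within-arm tests invite a misreading. Under equal true changes of 0.2 to 0.5 SD with r = 0.5, exactly one arm is significant in about 27% to 50% of trials at 25 per arm, and less often when changes are large.

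The SEM understates patient spread by a factor of 5.0 to 5.5 and obscures the SD, though it remains recoverable. The documents do not support any stronger reading, such as invalid tests, an irrecoverable SD or a compromised primary analysis.

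**What to change.** In section 2.15, for the continuous secondary outcomes:

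- Compare arms by ANCOVA with the outcome's preoperative value and the stratification factors of section 2.6 as covariates. Use a log scale for skewed markers.
- Use a repeated-measures model only where Table 1 gives an outcome two postoperative times, such as cardiac biomarkers at 12 h and 72 h. Inflammatory markers have only one (12 h).
- Report the between-group difference, or the ratio on the log scale, with a 95% confidence interval.
- Report mean (SD) in place of mean ± SEM.
- Drop the within-arm tests, or label them descriptive and not evidence of a treatment effect.

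No new data are needed, since the preoperative values are already scheduled. The cost is slightly more analysis work and a protocol modification, which section 2.17 says needs re-approval. As recruitment is ongoing (section 4), the change should be made before any data are unblinded.

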
Previous reports have suggested that acupuncture may be effective in preventing or alleviating SF-NR. However, it is not known whether electroacupuncture is effective in preventing or alleviating SF-NR in AMI patients undergo PCI, and high-quality randomized-controlled clinical trials (RCTs) are urgently necessary to investigate its efficacy and safety. Therefore, in this pilot RCT, we aim to investigate the potential benefits of intraoperative EA in reducing SF-NR during PCI in the AMI patients. The findings of this study are expected to lay the foundation for subsequent multicenter trials to establish the clinical safety and efficacy of intraoperative electroacupuncture as a novel strategy for managing SF-NR in AMI patients during PCI.

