### Study design

2.1

This pilot trial will adopt a single-center, blinded, randomized controlled design to determine the efficacy of intraoperative EA in preventing or reducing the incidence of SF-NR in patients with AMI undergoing PCI with standard PCI as control. The trial will follow the Chinese AMI management guidelines and the Declaration of Helsinki. This study has been approved by the Ethics Committee [Approval No. 2023-090-01]. All the study participants will be screened according to the inclusion and exclusion criteria. Finally, sixty eligible patients will be recruited and randomly assigned in a 1:1 ratio to either the EA group or the control group after obtaining informed consent. Patients in the acupuncture group will receive electroacupuncture during the standard PCI procedure, whereas patients in the control group will only receive the standard PCI procedure. The trial period will include the treatment duration from the time of hospital admission to the completion of PCI and a one-month follow-up period.

The protocol will be designed in compliance with the Standard Protocol Items for Randomized Trials (SPIRIT). The SPIRIT checklist is included in the Supplementary Appendix. The trial flow chart is shown in Figure 1. The study design schedule is shown in Table 1.

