### Adverse events

2.11

Adverse events (AEs) are unexpected symptoms, signs, or health conditions associated with the treatment. Pre-existing health conditions or diseases will be categorized as AEs only if they worsen post-treatment. Abnormal laboratory tests will be considered as AEs if they represent clinically significant symptoms that require treatment. Common adverse reactions to electroacupuncture include broken needles, fainting, bleeding, bruising, infection, swelling, and other discomforts following needle insertion such as post-acupuncture pain, nausea, palpitations, dizziness, headache, and insomnia. Detailed AE data will describe the symptoms, severity, onset date, relationship with study manipulation, measures taken in response (including drug combination, dosage, start and end times), intervention methods (such as ceasing acupuncture), duration, follow-up, and outcomes. Follow-up will be conducted immediately after enrolment, and timely reports will be submitted to the principal investigator until all the issues are resolved. The investigator has the authority to determine trial termination and provide economic compensation for study-related harm. Loss of follow-up will also be recorded if the investigator cannot obtain information regarding adverse events.

Serious Adverse Events (e.g., resulting in death, hospitalization, or disability) will be promptly reported to the principal investigator and the Medical Ethics Committee. The Case Report Form (CRF) will document the time of death and autopsy results, if applicable.

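### Section 2.15 does not exempt adverse events from its chi-square and P < 0.05 rule, a test that is unreliable for sparse events at 25 to 30 patients per arm and says little about harm when non-significant

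*Protocol article*

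**What the plan says.** The statistical analysis section (2.15) sets rules by type of data. For counts it says "Count data will be expressed as frequency (percentage) and analyzed using the chi-square test". The criterion is that P "< 0.05 will be considered as a statistically significant difference between groups". No exception is made for adverse events, and no interval is mentioned for any count outcome.

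The adverse events section (2.11) says "Common adverse reactions to electroacupuncture include broken needles, fainting, bleeding, bruising, infection, swelling", and adds other discomforts after needling such as post-acupuncture pain, nausea, palpitations and dizziness. It has each event recorded with its severity and its relationship to the study procedure. The safety assessments section (2.10) judges treatment safety from laboratory tests at admission and three days after the procedure. The Discussion includes adverse events among the items to be evaluated at completion.

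Controls receive standard PCI without needles; the Discussion confirms that there is no sham arm. On size, the sample size section (2.12) says "each group consisted of 25 patients and a total of 50 cases for the 2 groups", raised to 30 per group for dropout, and "instead of a formal sample size estimation, this trial will use a preliminary exploratory clinical pilot design".

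**The concern.** The number of patients with an adverse event is count data, so the general rule covers it unless something takes it out. Nothing in the article does. The only planned inference on harm would then be a chi-square P value from a very small trial.

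Three difficulties follow. First, adverse event tables here are likely to be sparse, and the chi-square approximation is poor when expected counts are low. Second, a P value above 0.05 at this size is compatible with a substantial excess of harm, yet is easily reported as no difference in adverse events. Third, some listed reactions cannot occur without a needle. For those the control rate is zero by design, and a test between arms answers no question.

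At stake is what the pilot passes on. The Introduction says trials are "urgently necessary to investigate its efficacy and safety" and expects the findings to support later multicentre trials. Those trials need a harm rate with its uncertainty more than a verdict of significance.

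**Working it through.** **Inputs from the article.** Allocation 1:1 (2.1); 25 per arm planned for analysis and 30 per arm recruited (2.12); chi-square at 0.05 (2.15), taken as two-sided because the article does not say. No continuity correction is specified, so uncorrected Pearson is the main case.

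**Inputs assumed.** The article gives no harm rate. EA rates of 5%, 10% and 20% against 0% in controls are used as a range, with 10% v 20% and 10% v 30% for events possible in both arms.

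**The plan's own figure.** 25 × (1 + 0.20) = 30 per arm, 60 in total. This reproduces the stated size, and the checks below use both 25 and 30.

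**Step 1: how many events the test needs.** With x events among n EA patients and 0 among n controls, Pearson chi-square = 2n(xn)² / [n · n · x · (2n − x)].
- n = 30, x = 3: 60 × 90² / (30 × 30 × 3 × 57) = 3.16, P = 0.076.
- n = 30, x = 4: 60 × 120² / (30 × 30 × 4 × 56) = 4.29, P = 0.038.
- n = 25, x = 4: 50 × 100² / (25 × 25 × 4 × 46) = 4.35, P = 0.037. Three events give P = 0.074.

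So at least 4 EA events are needed at either size.

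**Step 2: reliability at that threshold.** Four events in total give an expected count of 4 / 2 = 2 per arm. Fisher's exact P for 4 v 0 of 30 is 2 × C(30,4) / C(60,4) = 2 × 27,405 / 487,635 = 0.11, and the Yates-corrected P is 0.12. The significance verdict therefore depends on which version of the test is run. With Fisher or Yates, 6 events are needed.

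**Step 3: how often the result is non-significant.** With no control events, this is 1 − P(X ≥ 4), X binomial(n, p), for Pearson, and 1 − P(X ≥ 6) for Fisher or Yates.

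| Assumed EA rate (control 0%) | Pearson, n = 30 | Pearson, n = 25 | Fisher or Yates, n = 30 | Fisher or Yates, n = 25 |
|---|---|---|---|---|
| 5% | 93.9% | 96.6% | 99.7% | 99.9% |
| 10% | 64.7% | 76.4% | 92.7% | 96.7% |
| 20% | 12.3% | 23.4% | 42.8% | 61.7% |

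**Step 4: events possible in both arms.** Enumerating all 2 × 2 tables with Pearson and counting significance in the harmful direction, a rise from 10% to 20% is detected in 17% (n = 25) to 19% (n = 30) of trials, and a rise from 10% to 30% in 45% to 50%.

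**Step 5: what an interval would show.** Exact (Clopper-Pearson) two-sided 95% limits. For zero events the upper limit is 1 − 0.025^(1/n).
- 0/30: 0 to 11.6%; 0/25: 0 to 13.7%.
- 3/30: 2.1% to 26.5%; 3/25: 2.5% to 31.2%.

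Three events in 30 is what a 10% rate would produce on average. The test calls it non-significant (P = 0.076), while the interval shows that rates of up to about a quarter remain compatible with the data.

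**The case against.** The strongest reply is that 2.15 never mentions adverse events. It is a general paragraph in a condensed article, and a full protocol or analysis plan may treat safety separately. Sections 2.10 and 2.11 judge safety from laboratory results and record each event descriptively, including relatedness. Low power for rare events is inherent in a 60-patient pilot that makes no formal power claim. Much of this stands. That adverse events would be tested is a reading of a general rule, not an explicit statement. But the rule as published has no exception, and for sparse counts it fixes an unsuitable method.

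A reader might go further in two ways that the article does not support.

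- One inference is that needle harms as a class cannot occur in controls. Of the reactions named in 2.11, only broken needles and post-acupuncture pain strictly require needling. Bleeding, bruising, nausea, palpitations, dizziness and similar events can also follow PCI alone, and comparing arms on them is legitimate.
- Another is that the trial fails to answer a safety question it set itself. The Introduction speaks of the need for trials in general, gives this pilot's aim as potential benefit on slow flow/no-reflow, and leaves establishing safety to later multicentre trials. Frequencies, percentages and relatedness will be available, so safety is not left unreported.

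**Conclusion.** The point holds as a weakness in a stated rule that should be corrected before analysis. As written, 2.15 brings adverse events under a chi-square test whose verdict in sparse tables depends on the version used (P = 0.038 or 0.11 for 4 v 0 of 30). It would return a non-significant result in about 65 to 76% of trials under an assumed 10% v 0% excess. The range is 94 to 97% at an assumed 5% and 12 to 23% at an assumed 20%, so the problem concerns small and moderate excesses; with uncorrected Pearson a large one would usually be detected. These figures rest on the assumed rates, on no control events, and on uncorrected Pearson; Fisher or Yates makes non-significance more frequent. For events that need a needle, the between-arm test has no meaning at any sample size.

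**What to change.** In 2.15:

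1. Exempt adverse events from the chi-square rule.
2. Report events recorded as related to EA among needled patients only, as patients with at least one event out of patients needled, with an exact (Clopper-Pearson) 95% interval.
3. Report all-cause adverse events and serious adverse events by arm, as risk differences with 95% intervals by a method suited to sparse data, without a significance verdict.
4. State that a non-significant difference, or zero events, will not be read as evidence of safety, noting that 0 of 30 excludes only rates above about 12%.

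The cost is a few sentences and a little table work. No new data or patients are needed, since 2.11 already has relatedness recorded. The safety statement will read less favourably than one based on a non-significant P value.
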